One key mechanism underlying the heavy metal toxicity is oxidative stress, which causes damage to lipids, proteins, and DNA. Biomarkers such as malondialdehyde (MDA) and 8-hydroxy-2’-deoxyguanosine (8-OHdG) reflect oxidative damage and are commonly elevated in metal-exposed individuals  [7-9]. Additionally, heavy metals can disrupt DNA methylation [10], an epigenetic process critical for normal fetal development, thereby contributing to adverse pregnancy outcomes  [11-13]. Heavy metals such as Pb, Cd, and Hg exert toxic effects partly through the generation of reactive oxygen species (ROS), leading to oxidative stress [14]. This imbalance between ROS and antioxidant defenses causes damage to cellular lipids, proteins, and DNA, as reflected by increased levels of oxidative stress biomarkers such as 8-OHdG and MDA [15,16]. These molecular injuries are particularly harmful during pregnancy as they disrupt placental development and fetal growth processes [17,18]. Studies have shown that oxidative stress plays a central role in the pathogenesis of adverse pregnancy outcomes [19], including preeclampsia [20], miscarriage [21], LBW [22], and preterm birth [23]. A previous study by Zinia et al [24] indicated that high maternal blood Cd levels (0.62 μg/L in early pregnancy and 0.70 μg/L in late pregnancy), Pb levels (early pregnancy 0.74 vs late pregnancy 0.70 μg/dL), and Hg levels (early pregnancy 2.37 vs late pregnancy 1.95 μg/L) were inversely associated with birth weight.

Although certain micronutrients such as zinc and cysteine may assist in the detoxification of heavy metals [25], their use as targeted interventions remains inconsistent and often inaccessible to at-risk populations. Therefore, *Moringa oleifera* has emerged as a promising, locally available resource. Moringa contains flavonoids, phenolic acids, glucosinolates, and phytates and exhibits antioxidant and metal-chelating properties that can mitigate the toxic effects of heavy metals [26,27]. These compounds have been shown in in vitro and in vivo studies to counteract oxidative stress and inflammation induced by toxicants, including heavy metals.

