Beyond laboratory studies, there is growing evidence of moringa’s nutritional and therapeutic effects in humans. Moringa leaf supplementation has shown improvements in hemoglobin levels in children with iron deficiency anemia and increased breast milk production in postpartum women [28]. In a clinical trial, moringa leaf powder (0.5 g/d) led to significant reductions in body weight, blood pressure, and lipid profiles in overweight individuals with hyperlipidemia [29]. In pregnant women, moringa has emerged as a beneficial supplement, particularly in enhancing maternal and neonatal health. A study in southern Ethiopia found that the consumption of moringa was associated with an increase in birth weight by approximately 115.77 g, suggesting its potential role in improving neonatal outcomes [30]. Moringa leaves are rich in iron, which is crucial for preventing anemia during pregnancy. A study in Karachi reported that pregnant women consuming moringa leaf powder showed hemoglobin levels of 9.09 g/dL in the third trimester, indicating a potential benefit in managing anemia [31]. No contraindications for moringa use during pregnancy were reported in the reviewed studies, suggesting it is generally safe for consumption [32].

Although moringa grows abundantly in many regions of Indonesia, particularly in Makassar, it is typically consumed sporadically as a vegetable, with unmeasured doses and limited awareness of its therapeutic potential. In other areas, such as Java, consumption is even more limited. These factors underscore the need for a standardized, supplement-based intervention to realize public health benefits of moringa. Despite the well-documented risks of heavy metal exposure during pregnancy, interventional studies remain scarce, particularly in Indonesia. To date, there has been no clinical trial examining the efficacy of moringa in the detoxification of heavy metals among pregnant women. In addition, most existing research is observational and lacks an evaluation of strategies to reduce maternal metal levels or oxidative damage. This study seeks to address this gap by investigating the effect of standardized *M. oleifera* supplementation on heavy metal level and oxidative stress reduction in pregnant women. We hypothesize that pregnant women receiving *M. oleifera* supplementation will have significantly lower blood heavy metal concentrations and oxidative stress biomarkers than before receiving.

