#### Capsule Supplement Production

The dry extract was ground again using mesh 100 to obtain a fine extract powder. This powder was then mixed with corn starch as a filler in a 4:1 ratio (400 mg of moringa extract and 100 mg of corn starch per capsule). Each capsule contained 400 mg of moringa leaf extract. Participants in the intervention group received 2 capsules twice daily (totaling 2000 mg/d) for a period of 8 weeks, beginning immediately upon enrollment (between gestational weeks 20‐32). In cases where participants gave birth before completing the 2-month supplementation period, they were instructed to continue consuming the remaining *M. oleifera* supplements until the full course was completed. This approach aimed to ensure consistency in the intervention dosage, regardless of the timing of delivery, and to maintain the study’s internal validity.

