### Intervention Group

In addition to receiving iron capsules, which are standard supplements provided by the health centers as part of the national prenatal care program, participants in the intervention group also received *M. oleifera* extract supplementation at a dose of 2000 mg/day, administered as 2 capsules taken twice daily (totaling 2000 mg/day) for a continuous period of 8 weeks. Supplementation began immediately upon enrollment, which occurred between gestational weeks 20 and 32. Therefore, the regimen lasted from the time of enrollment until 8 weeks later, typically ending between weeks 28 and 40 of gestation. For participants enrolled in the late third trimester who delivered before completing the full 8 weeks, they were instructed to continue consuming the remaining *M. oleifera* supplements until the full course was completed. This approach aimed to ensure consistency in the intervention dosage, regardless of the timing of delivery, and to maintain the study’s internal validity.

To support adherence, we collaborated with health cadres at each participating health center. The cadres will be responsible for supervising, reminding, and ensuring that the mothers consistently take the moringa capsules. A WhatsApp group was established specifically for the cadres to facilitate regular communication, provide reminders, and monitor the supervision process throughout the 8-week supplementation period. We have also added a simple adherence log that will be maintained by the cadres, documenting capsule intake daily based on direct questioning or observation. These dual approaches—cadre monitoring and pill counts—will allow us to triangulate adherence data and better distinguish true intervention effects from variability due to compliance.

Participants will be actively monitored for adverse events throughout the 8-week intervention period. At the follow-up visit, participants will be asked about any symptoms or side effects experienced, using a structured checklist and open-ended questions. Specific adverse events of interest include gastrointestinal discomfort (nausea, vomiting, and diarrhea), allergic reactions (skin rash and swelling), and general intolerance to the supplement.

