#### Safety and Tolerability of *M. oleifera*

Hypothesis: *M. oleifera* supplementation will be safe for pregnant women, with no significant adverse effects reported during the intervention period. Hence, the expected results are as follows: (1) Minimal to no adverse effects in the group receiving *M. oleifera* supplementation. (2) This safety profile is consistent with previous studies indicating that 2000 mg/day is safe for pregnant women.

This will provide further evidence that *M. oleifera* is a safe supplement for pregnant women, supporting its use in future clinical applications and maternal health programs.

In the final analysis, changes in heavy metal levels (Pb, Cd, and Hg) will be reported individually, as well as in aggregate if appropriate. Similarly, biomarkers of oxidative stress (8-OHdG and MDA) will be analyzed and reported separately. While the study is not powered for definitive subgroup comparisons, exploratory reporting by relevant characteristics (eg, trimester, nutritional status, and baseline exposure level) will be presented to generate hypotheses for future studies.

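### The protocol cites falls in body weight and blood pressure with moringa but plans to track neither, so its safety conclusion cannot cover symptomless changes in them

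*Protocol article*

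**What the plan says.** The Introduction of the protocol article cites human evidence that "moringa leaf powder (0.5 g/d) led to significant reductions in body weight, blood pressure, and lipid profiles in overweight individuals with hyperlipidemia". It presents this as a therapeutic benefit.

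The Intervention Group section lists the targeted events: "Specific adverse events of interest include gastrointestinal discomfort (nausea, vomiting, and diarrhea), allergic reactions (skin rash and swelling), and general intolerance to the supplement". On how they are collected, it says that at the follow-up visit "participants will be asked about any symptoms or side effects experienced, using a structured checklist and open-ended questions". It adds that serious adverse events and pregnancy complications are recorded and reviewed by the study physician, that maternal and fetal complications are documented, and that all safety data go into the case report forms and the final report.

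The Data Collection section names the measurements repeated after 8 weeks: blood heavy metals, 8-OHdG and MDA. The Data Analysis section mentions BMI only as a possible subgroup factor. The Control Group section describes no adverse-event capture.

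The section Safety and Tolerability of M. oleifera expects "Minimal to no adverse effects in the group receiving" the supplement, and says this will be further evidence that moringa is safe for pregnant women. The section Principal Anticipated Findings repeats the aim of confirming safety and tolerability.

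**The concern.** The article reports two measurable effects of moringa on maternal physiology, then plans a safety assessment in pregnant women that measures neither. Weight and blood pressure can both shift without the woman noticing, so asking about symptoms is a poor way to find a change in them.

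What is at stake is the reach of the safety conclusion. A final report could state that few or no adverse effects occurred although these two variables had never been examined. The Dissemination Plan foresees integrating the results into maternal health programs, so a safety statement wider than the data behind it would matter in practice.

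**Working it through.** **1. Capture routes set against the two cited effects.**

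| Route (protocol article section) | Symptomless fall in blood pressure | Symptomless slower weight gain |
|---|---|---|
| Listed events of interest (Intervention Group) | not named | not named |
| Checklist and open-ended questions (Intervention Group) | only if felt and reported | only if noticed and reported |
| Serious events and complications (Intervention Group) | only if it leads to a recorded event | only if it leads to a recorded event |
| Repeated measurements at 8 weeks (Data Collection) | not named | not named |
| Subgroup factors (Data Analysis) | not named | BMI, as a stratifier only |

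No stated route records a shift in either measured value. Symptomatic or serious consequences would be caught.

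**2. Comparator.** Adverse-event monitoring is described under Intervention Group, and Control Group is silent on it. As the article stands, there is no stated control-arm rate or mean. Both variables may also change over 8 weeks of pregnancy without any supplement, so values from the intervention arm alone could not be read as a supplement effect.

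**3. Is the fix feasible?** Participant Recruitment places follow-up blood collection at a routine visit for the intervention group and at the next scheduled antenatal visit for controls. No new visit is needed. That these visits record blood pressure and weight is an assumption; the article does not say so.

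**4. Precision the fix could deliver.** Results reports 26 women per group to date. For a difference in means, the 95% CI half-width is t(0.975, 50 df) × √(2/26) × SD = 2.009 × 0.277 × SD ≈ 0.557 SD. The documents give no SDs, so these are assumptions:
- Systolic pressure, SD 10 mmHg: 0.557 × 10 ≈ 5.6 mmHg.
- Weight gain, SD 2 to 3 kg: 0.557 × 2 ≈ 1.1 kg to 0.557 × 3 ≈ 1.7 kg.

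These half-widths are optimistic. They treat 52 women as independent, whereas three centers were assigned to each arm without randomization. The comparison can be exploratory only.

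**5. A separate dose discrepancy.** The Intervention Group section states "extract supplementation at a dose of 2000 mg/day, administered as 2 capsules taken twice daily". Capsule Supplement Production gives "400 mg of moringa extract and 100 mg of corn starch per capsule".
- Capsule mass: 2 × 2 × (400 + 100) = 2000 mg/day, which reproduces the stated figure as total capsule content.
- Extract: 2 × 2 × 400 = 1600 mg/day, which does not match 2000 mg/day of extract.

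The two sections must be reconciled. The point on safety capture does not depend on which figure is meant.

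**The case against.** The strongest reply is that this is an omission from a condensed article. The list is introduced as non-exhaustive, the checklist itself is not shown, open-ended questions accompany it, serious events and complications are recorded, and the case report forms may hold routine antenatal values. The article also calls its findings preliminary and hypothesis-generating.

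Much of that stands. The stated safety capture is wider than the three listed groups of events, and the full protocol may contain more. But none of the stated routes records a measured value, and the article itself commits to a general conclusion of safety in pregnancy. That mismatch is visible in the text shown.

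A reader might also infer more than the documents support:
- **That the protocol expects these effects in its participants.** It does not. The cited trial was in overweight people with hyperlipidemia. Principal Anticipated Findings assumes that antioxidant and chelating mechanisms will carry over, and says nothing of blood pressure or weight.
- **That the trial gives four times an active dose.** 2000/500 = 4 (or 1600/500 = 3.2) compares leaf powder with a freeze-dried water extract. It is a ratio of milligrams, not of exposure.
- **That haemoglobin or essential minerals should be at risk.** The Introduction says "Moringa contains flavonoids, phenolic acids, glucosinolates, and phytates and exhibits antioxidant and metal-chelating properties", but only in connection with heavy-metal toxicity. The same section cites improved haemoglobin in anemic children and iron-rich leaves, which points the other way.

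**Conclusion.** The point holds in a limited form. The protocol article cites reductions in body weight and blood pressure with moringa, names neither as an event of interest or follow-up measurement, and describes no adverse-event capture in controls. Its planned safety conclusion therefore cannot speak to symptomless changes in either variable.

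The size is a matter of coverage: two cited effects, neither measured. No harm is shown or quantified. Whether these effects occur in pregnant women at all is unknown from the documents. The finding assumes that the unshown checklist and forms do not already collect both values in both arms; if they do, it reduces to stating this and reporting the comparison.

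**What to change.** - Abstract blood pressure and body weight from the routine antenatal records at baseline and at the 8-week visit, in both arms, wherever the records hold them.
- Report between-arm differences with confidence intervals, described as exploratory because allocation was nonrandomized and by center.
- Analyse women who delivered before week 8 separately, using their last antenatal value, so that pregnant and postpartum measurements are not mixed.
- State whether adverse events are collected in the control arm in the same way as in the intervention arm.
- If the values cannot be obtained, restrict the conclusions in Safety and Tolerability of M. oleifera and in Principal Anticipated Findings to symptomatic tolerability and recorded complications.
- Separately, reconcile the stated daily amount of extract with the capsule content.

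The cost is two values per woman per time point, with no new visit or blood draw. The downside for the sponsor is that the resulting safety statement may be less favourable or narrower than now planned.

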### Participant Recruitment

This research has been conducted in Makassar City, specifically at 6 community health centers where expectant women receive prenatal services. The 6 selected community health centers are located in areas with varying environmental characteristics, including industrial zones, regions near landfill sites, and coastal areas. While the types of pollution sources differ, all sites share a common feature: exposure to potential environmental contaminants. Each represents an urban setting with a plausible risk of heavy metal exposure through air, water, and food pathways. Thus, despite differences in specific pollution types, the study sites are considered comparable in terms of overall environmental risk exposure. This selection strategy ensures that the intervention and control groups are drawn from communities facing similar environmental health challenges. Moreover, such variation may enhance the generalizability of findings across different urban pollution contexts. Three centers were assigned as intervention sites and 3 as control sites based on operational convenience and to avoid information spillover between groups.

The study will include 59 pregnant women in each group of intervention and control who underwent an examination at health centers in Makassar and fulfilled the following inclusion criteria: (1) pregnancy during the second or third trimester, (2) intention to deliver in Makassar, (3) living in Makassar for a period exceeding 1 year, and (4) blood levels of Hg, Pb, or Cd exceeding the reference value. Participants will be excluded based on self-report during interview if they (1) are having twin pregnancy, (2) had known chronic medical conditions, such as diabetes, cancer, kidney diseases, (3) are taking other antioxidant or mineral supplements beyond standard care, (4) are diagnosed with micronutrient deficiencies, (5) relocate during the intervention period, and (6) are unwilling to comply with follow-up procedures.

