Any serious adverse events, including pregnancy complications such as preeclampsia, gestational diabetes, preterm labor, or hospitalizations, will be recorded and reviewed by the study physician. Although these are not primary outcomes, maternal and fetal complications will be documented to ensure a complete safety profile.

Prior evidence suggests that *M. oleifera* supplementation at a dose of 2000 mg/day is safe for human use, including during pregnancy. However, all safety data will be recorded in participant case report forms, monitored by the study team, and summarized in the final report.

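### The only stated adverse-event window is the 8-week course, ending at gestational weeks 28 to 40, which cannot support a complete maternal and fetal safety profile or a general conclusion of safety in pregnancy

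*Protocol article*

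**What the plan says.** Under Intervention Group, the protocol article states that "Participants will be actively monitored for adverse events throughout the 8-week intervention period". It adds that "At the follow-up visit, participants will be asked about any symptoms or side effects experienced". On timing it says "Supplementation began immediately upon enrollment, which occurred between gestational weeks 20 and 32", with the regimen "typically ending between weeks 28 and 40 of gestation".

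The same section says that serious adverse events, "including pregnancy complications such as preeclampsia, gestational diabetes, preterm labor, or hospitalizations, will be recorded and reviewed by the study physician". It then says that "maternal and fetal complications will be documented to ensure a complete safety profile". These sentences on serious events carry no end date of their own.

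The Safety and Tolerability section hypothesises that the supplement will be safe, "with no significant adverse effects reported during the intervention period". It expects the result to be further evidence of safety for pregnant women and to support use in maternal health programs. Principal Anticipated Findings says that birth weight and gestational age are not evaluated.

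No safety contact at or after delivery is described, and no observation of the newborn. The Control Group section describes no adverse-event monitoring. Women who deliver during the course are told to finish the capsules.

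**The concern.** A window and a promise are both stated, and they do not fit. The named events include preterm labor and preeclampsia, and the promise extends to fetal complications. For any woman who enrols early, stated monitoring ends weeks before delivery. Events after that point, and most fetal or neonatal complications that show at birth, have no described route into the data.

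What is at stake is the safety conclusion, not the biomarker results. A low count of pregnancy complications would partly reflect the length of observation, and the Safety and Tolerability section would read it as evidence that the supplement is safe in pregnancy. How much of a pregnancy is observed also depends on gestational age at enrolment, so a plain count mixes women with very different observed fractions.

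**Working it through.** **Inputs from the protocol article (Intervention Group).** Enrolment week *e* lies between 20 and 32. The course, and with it the stated monitoring, lasts 8 weeks.

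**Assumptions, not in the document.** The preterm period ends at week 37. The distribution of *e* within weeks 20 to 32 is unreported, so four patterns are tried. Week 40 stands in for delivery where time to delivery is needed.

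**1. Reproduce the stated end of the course.** 20 + 8 = 28 and 32 + 8 = 40, which matches the stated weeks 28 to 40.

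**2. Who leaves before week 37?** *e* + 8 < 37 gives *e* < 29.

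**3. What share is that?**
- Uniform on 20 to 32: (29 − 20)/(32 − 20) = 9/12 = 75%.
- Triangular, peak at week 20: 1 − (3/12)² = 0.9375, about 94%.
- Triangular, peak at week 26: 1 − 2 × (3/12)² = 0.875, about 88%.
- Triangular, peak at week 32: (9/12)² = 0.5625, about 56%.

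The share falls below half if most women enrolled after week 29.

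**4. What is observed and what is missed?** Weeks observed before week 37 are min(8, 37 − *e*). Weeks missed before week 37 are max(0, 29 − *e*). Weeks missed before week 40 are 32 − *e*.

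| Enrolment week | End of window | Observed before 37 | Missed before 37 | Missed before 40 |
|---|---|---|---|---|
| 20 | 28 | 8 | 9 | 12 |
| 24 | 32 | 8 | 5 | 8 |
| 28 | 36 | 8 | 1 | 4 |
| 29 | 37 | 8 | 0 | 3 |
| 32 | 40 | 5 | 0 | 0 |

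Every woman is therefore observed for 5 to 8 preterm weeks.

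**5. Average coverage.** Under uniform enrolment, the mean share of the time from enrolment to week 37 that is covered is [8 ln(17/8) + 3]/12 = (6.03 + 3)/12 = 0.753, about 75%. Across the four patterns it is 64% to 86%. To week 40, uniform enrolment gives 8 ln(20/8)/12 = 0.611, about 61%, and the patterns give 52% to 70%. Mean time missed before week 40 is 6 weeks under uniform enrolment and 4 to 8 weeks across the patterns.

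**6. Set against the promise.** The window reaches week 40 only for a woman enrolled at week 32. For one enrolled at week 20 it stops 12 weeks short. Complete documentation of maternal and fetal complications does not follow from it.

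**The case against.** A reader might infer that most women leave monitoring before preterm labor or preeclampsia could have occurred. The document's figures do not support that. Monitoring lies within weeks 20 to 40, every woman contributes at least 5 preterm weeks, and the protocol itself expects some deliveries inside the course. Under uniform enrolment about three quarters of the time to week 37 is covered. For preeclampsia the document gives no timing. For the same reason, it would go too far to say that few complications would be seen largely because observation stopped.

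Nor is it a stated fact that most women are affected: that rests on an unreported enrolment distribution and an assumed threshold.

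It can also be said that the 8-week sentence introduces a tolerability checklist, that the serious-event sentences have no cut-off, and that a journal article may leave the reporting period to the full protocol. This stands in part, since it is an inference that serious-event recording stops at 8 weeks. But the completeness claim is made in the article, and the only window beside it is the shorter one. If recording is meant to run to delivery, the window needs to say so; if it is not, the claim is too wide.

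The article does hedge. The safety hypothesis refers to the intervention period, and Strengths and Limitations restricts conclusions on long-term maternal and fetal health. Those cautions do not narrow the expected conclusion that the supplement is safe for pregnant women. No between-arm safety test is stated, so distortion of such a comparison by enrolment timing is a secondary matter.

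**Conclusion.** The point holds in this form: the one stated adverse-event window supports statements about events during the 8-week course, but not a complete maternal and fetal safety profile or a general conclusion of safety in pregnancy. That the course ends at weeks 28 to 40 is the protocol's own figure. The share of women who leave while preterm labor is still possible is conditional on the week-37 threshold and on enrolment: 75% if uniform, about 56% to 94% under the other patterns tried, and below half if most enrolled after week 29. Capture of preterm events is partial, not absent, and weakest for early enrollees. Complications at delivery are mostly outside the window. The heavy-metal and oxidative-stress analyses are unaffected.

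**What to change.** Reconcile the monitoring sentence, the completeness claim and the Safety and Tolerability conclusion in one of two ways.

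- **Extend the record.** State that the named serious events and fetal or neonatal complications are recorded through delivery, or to the last capsule if delivery comes first. Take them from existing antenatal and delivery records, use the same window in both arms, and report them as safety data only, not as efficacy outcomes.
- **Narrow the claim.** Where records or consent do not allow this, replace the completeness claim with a statement that events were recorded during the 8-week course only, and limit the safety conclusion to that window.

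The first option costs one record look-up or call per woman: 52 for the 26 per group reported as having participated, and up to 118 for the 59 per group given under Participant Recruitment. Data collection began in July 2024, so for women already followed this is retrospective retrieval, with ethics notification and possibly a question of consent. Some records will be missing, though the inclusion criterion "intention to deliver in Makassar" should help. The second option costs only a change of wording.

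### Women who deliver mid-course keep taking capsules, but the safety record is scoped to mother and fetus, so newborn events in that time are not assured of capture

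*Protocol article*

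**What the plan says.** Three parts of the protocol article bear on this.

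- **Postpartum use.** The section on capsule production covers delivery before the end of the course: "In cases where participants gave birth before completing the 2-month supplementation period, they were instructed to continue consuming the remaining" supplements to the end of the course. The Intervention Group section repeats the rule: "they were instructed to continue consuming the remaining *M. oleifera* supplements until the full course was completed". Both give consistent dosage and internal validity as the reason.
- **Timing.** "Supplementation began immediately upon enrollment, which occurred between gestational weeks 20 and 32", with courses "typically ending between weeks 28 and 40 of gestation".
- **Safety recording.** "Participants will be actively monitored for adverse events throughout the 8-week intervention period". At follow-up the women are asked about their own symptoms, by structured checklist and open-ended questions. Any serious adverse event is recorded and reviewed by the study physician; the examples given are pregnancy complications and hospitalizations. The scope is then put as follows: "maternal and fetal complications will be documented to ensure a complete safety profile". Safety data go into the participants' case report forms.

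Under Safety and Tolerability, the article expects minimal to no adverse effects and adds: "This safety profile is consistent with previous studies indicating that 2000 mg/day is safe for pregnant women".

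**The concern.** The protocol deliberately creates a period in which a woman who has delivered is still taking the extract. In that period the child is a newborn, not a fetus. The persons monitored are the participants, that is, the women. Every named adverse event is maternal or obstetric, and the stated scope is maternal and fetal. Staff who follow the text have no instruction to ask about the baby.

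A newborn illness, admission or death while the mother is still supplemented could therefore go unrecorded, or be recorded for some women and not for others, depending on who volunteers it. The final report could then describe a complete safety profile without knowing whether such events occurred. The issue is who is observed during the 8 weeks, not how long the safety window is.

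**Working it through.** **Step 1: reproduce the stated end of course.** Entry week plus 8 gives 20 + 8 = 28 and 32 + 8 = 40. This matches the stated range of weeks 28 to 40.

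**Step 2: can postpartum use arise within that window?** Weeks of capsules left at delivery = (entry week + 8) − delivery week. The article gives no delivery weeks, so those below are illustrative. The last column assumes entry spread evenly over weeks 20 to 32: share = (40 − delivery week) / 12.

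| Delivery week | Weeks left if entered at week 32 | Share of women with capsules left |
|---|---|---|
| 34 | 6 | 6/12 = 50% |
| 37 | 3 | 3/12 = 25% |
| 38 | 2 | 2/12 = 17% |
| 39 | 1 | 1/12 = 8% |
| 40 | 0 | 0% |

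So it can arise without any departure from the stated window.

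**Step 3: a rough size.** Let delivery be normal with mean μ and SD σ (assumed), with entry again uniform over weeks 20 to 32. Course end is then uniform over weeks 28 to 40. With a = (40 − μ)/σ, and with delivery before week 28 negligible,

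share = σ[φ(a) + aΦ(a)] / 12.

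- μ = 39.5, σ = 1.3: a = 0.385; 1.3 × (0.3705 + 0.385 × 0.6497) = 0.807; 0.807/12 = 6.7%.
- μ = 39.0, σ = 1.5: a = 0.667; 1.5 × (0.3194 + 0.667 × 0.7475) = 1.227; 1.227/12 = 10.2%.
- μ = 38.5, σ = 1.8: a = 0.833; 1.8 × (0.2819 + 0.833 × 0.7977) = 1.704; 1.704/12 = 14.2%.

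For the 26 mothers per group reported so far, this is 26 × 0.067 = 1.7 to 26 × 0.142 = 3.7, or about 2 to 4 supplemented women. For the 59 per group named under Participant Recruitment, it is 59 × 0.067 = 4.0 to 59 × 0.142 = 8.4, or about 4 to 8.

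The result depends on entry. If all women entered at weeks 28 to 32, the same delivery assumptions give about 20 to 41%. The Intervention Group section also speaks of women enrolled late in the third trimester, which is hard to square with entry closing at week 32. Any later entry would lengthen the overlap.

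**Step 4: set the treated time against the safety record.**

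| Period | Taking capsules | Events the text asks for |
|---|---|---|
| Before delivery | Woman | Woman's symptoms, serious events, maternal and fetal complications |
| After delivery, course unfinished | Woman, by instruction | Woman's symptoms, serious events; nothing on the newborn by name |

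**The case against.** A reader might infer that newborn events are excluded from the record. The text does not support that. Serious adverse events are introduced with open wording, the items listed are examples, hospitalizations are among them, and the follow-up visit includes open-ended questions. A newborn admission could be captured. What remains is that capture is possible but not assured.

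A reader might also infer that the planned conclusion claims safety for newborns or during breastfeeding. It does not. The hypothesis under Safety and Tolerability, and the aim restated in the Discussion, concern pregnant women. The Discussion says that birth weight and other clinical outcomes are not assessed and that the findings are hypothesis-generating. This objection stands and limits the point to the claim of completeness and to what is collected.

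The strongest objection is that a journal article condenses a fuller protocol, that the checklist itself is not reproduced, and that it may contain newborn items. That is possible. But the article does not leave the scope open: it states a maternal and fetal scope, ties it to completeness, and twice describes capsule use after birth. If the full protocol covers newborns, the published sentence still needs correcting.

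Finally, the two instructions can both be followed, so this is a mismatch of scope and not a logical contradiction. The number affected is also probably small. Both points are fair.

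**Conclusion.** The point holds in a limited form. The article instructs use of the capsules after birth, while its stated safety scope stops at the woman and the fetus. Newborn events during that time are not assured of capture, and the profile should not be called complete.

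The number of women concerned cannot be derived from the documents. About 7 to 14% follows only under uniform entry over weeks 20 to 32 and mean delivery at 38.5 to 39.5 weeks (SD 1.3 to 1.8), all of them assumptions. On that basis it is a minority, too few for any inference about newborn safety. The reason to act is orderly recording of rare but serious events, which should be done but does not threaten the primary analysis. Whether capsules should continue after delivery is a clinical matter and is not judged here.

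**What to change.** Reconcile the continuation rule (capsule production and Intervention Group sections) with the safety scope (Intervention Group section):

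1. Add newborn illness, hospital admission and death to the existing follow-up checklist for every woman who has delivered by that visit.
2. Send these events through the study-physician review already planned.
3. List separately the newborns whose mothers took capsules after birth. A listing is enough at these numbers.
4. By February 2025, 26 mothers per group had taken part and laboratory work had reached the second step, so some follow-up visits are probably past. For those women, use available records, or state in the report that newborn events were not collected.
5. Where newborn events were not collected, remove the claim of completeness and keep the safety conclusion to maternal tolerability and use during pregnancy.

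The cost is a few form items and a protocol and ethics notification, with no new visit for women still to be seen. For women already seen, there is the added work of looking up records, or a sentence of disclosure. Dose, schedule and the continuation rule are left as they are.
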